### Statistical analysis

#### Sample size calculation

We calculated the sample size for this study using a superiority categorical variable sample size formula. We assumed the improvement of perfusion defect size as >25% in adenosine-stress CMR from baseline to three months after udenafil treatment. According to the researcher’s intuition, we assumed the improvement of perfusion defect as 2% in the control group. If we applied two tails, an 80% power, an α-level of 0.05, and 10% dropout rate, we would need a total of 76 patients: 38 patients in the udenafil treatment arm and 38 patients in the control arm.

The prevalence of variant angina in Asian population is reported to be between 1 to 5% [14]. For a total of 76 patients, 4 patients with variant angina will possibly be enrolled in this study. In order to achieve scientifically robust results, we will enroll a total of 80 patients (40 patients in the udenafil treatment arm and 40 patients in the control arm).

#### Statistical analysis

For comparison between the udenafil treatment and the control group, we would use student’s t-test for continuous variables and χ^2^-test for categorical variables. To evaluate improvement of perfusion defect size >25% between udenafil treatment and control group, we would analyze using Fisher’s exact test. The difference in the continuous outcome between the experimental and control group will be assessed using generalized linear models. Frequency differences will be tested using χ^2^-test or Fisher’s exact test. We will be analyzing this data using an intention-to-treat analysis. All randomized patients will be included in the analysis. A *P* value of less than 0.05 will be considered statistically significant.

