**Table 1 Tab1:** **Endpoints**

	Endpoint details
Primary endpoint	>25% improvement in perfusion defect size in adenosine-stress CMR from baseline to three months after udenafil treatment
Secondary endpoints	<25% improvement in perfusion defect size in adenosine-stress CMR from baseline to three months after udenafil treatment
	Decrement of frequency of chest pain
	Improvement of ST-depression in stress test
	Improvement of Duke score in stress test
	Improvement of QoL assessment by SF-36 questionnaire
	Improvement of sexual dysfunction assessment by BISF-W self-questionnaire
	Improvement of biomarkers for endothelial function

CMR*;* Cardiac magnetic resonance image, QoL; Quality of life.

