**Table 3 Tab3:** **Trial process chart**

Visit	Visit 1	Visit 2	Visit 3	Visit 4	Visit 5	Visit 6	Visit 7
Status	Screening	Baseline					Follow-up phase
Week	−4 ~ 0	0	1 (±3 day)	4 (±7 day)	8 (±7 day)	12 (±7 day)	16
Informed consent	●						
Inclusion/exclusion criteria	●						
Baseline characteristics	●						
Risk factors	●						
Medical history	●						
Past medication history^1^	●						
Family history	●						
Randomization		●					
Physical examination	●					●	
Vital signs	●	●		●	●	●	
Height/weight^2^	●	●		●	●	●	
Blood analysis^3^	●					●	
Pregnancy test^4^	●					●	
ECG	●					●	
Echocardiography	●					●	
Exercise test	●					●	
CMR^5^	●					●	
CAG or CCTA	●						
SF-36 questionnaire	●					●	
BISF-W self-assessment questionnaire	●					●	
Case drug distribution		●		●	●		
Case drug collection				●	●	●	
Trial evaluation							
Adverse events	●	●	●	●	●	●	●
Patient’s compliance			●	●	●	●	
Concomitant medications^6^		●	●	●	●	●	

CMR; Cardiac magnetic resonance image, CAG; Coronary angiography, CCTA; Coronary CT angiography, ECG; Electrocardiogram.

^1^The participant’s usual medication regimen continued unchanged throughout study duration.

^2^Check weight only after Visit 2.

^3^CBC: WBC, Hemoglobin, Hematocrit, Platelet; Chemistry: Total protein, Albumin, Globulin, Total bilirubin, AST; aspartate aminotransferase, ALT; alanine transaminase, ALP; alkaline phosphatase, BUN; blood urea nitrogen, Creatinine, Uric acid; Electrolyte: Na, K, Cl; NT-proBNP; N-terminal of the prohormone brain natriuretic peptide; hs-CRP; high-sensitivity c-reactive protein.

(NT-proBNP, hs-CRP: check visit 1 and visit 5).

^4^Women of child-bearing age.

^5^Stop all medications three days before CMR.

^6^Concomitant medications: beta-blockers, calcium channel blockers, angiotensin converting enzyme inhibitors, angiotensin receptor blockers, statin, and trimetazidine.

During follow-up visits all adverse events including chest pain, headache, and so forth, will be documented. Serious adverse events will be immediately reported to the principal investigator. To ensure the quality of this trial, the clinical monitors will survey and document the trial process once a month in each participating hospital. Patient dropouts and the reasons, and patients’ compliance will be recorded at three months after randomization.

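### Two methods, a t-test and a generalized linear model, are named for continuous between-arm comparisons; neither is said to govern the secondary endpoints, and no baseline term is stated although baselines are collected

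*Protocol article*

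**What the plan says.** In the Statistical analysis section of the protocol article, the opening sentence deals with comparing udenafil with control and names Student's "t-test for continuous variables", with a χ² test for categorical ones. The next sentence gives the primary endpoint its own test: "To evaluate improvement of perfusion defect size >25% between udenafil treatment and control group, we would analyze using Fisher’s exact test". The third returns to continuous data: "The difference in the continuous outcome between the experimental and control group will be assessed using generalized linear models". No family, link or covariate is given for that model, and nothing says how it relates to the t-test. The section closes with one threshold for everything: a P "value of less than 0.05 will be considered statistically significant".

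Table 1 lists the secondary endpoints that are, or can be, continuous: ST depression, Duke score, SF-36, BISF-W and biomarkers of endothelial function. They are worded as improvements, for example "Improvement of QoL assessment by SF-36 questionnaire". That wording suggests a change from baseline but does not fix the scale.

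Table 3 marks the "SF-36 questionnaire", the "BISF-W self-assessment questionnaire", the exercise test, CMR and blood analysis at screening and again at week 12. Its third footnote, however, places NT-proBNP and hs-CRP at visits 1 and 5, and visit 5 is week 8.

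**The concern.** The same two arms and the same type of variable are given two methods, with no rule of precedence. A two-sample t-test cannot carry a covariate. If it is the method for the secondary endpoints, the baseline values already collected are either unused (final values compared) or used inefficiently (change scores compared). If the model is the method and contains baseline, the t-test still stands in the plan as a second route to a p-value for the same endpoint. With about 36 evaluable patients per arm, precision is scarce, and the trial's evidence on quality of life, exercise findings and sexual function rests on these analyses.

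**Working it through.** **The plan's own figure.** The only calculated size is for the binary primary endpoint. Its settings are given as "If we applied two tails, an 80% power, an α-level of 0.05, and 10% dropout rate", with 2% in control. The responder rate under udenafil is not stated plainly; 25% is inferred because it reproduces the total. With pooled variance and no continuity correction:

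n = [1.96·√(2·0.135·0.865) + 0.842·√(0.02·0.98 + 0.25·0.75)]² / 0.23² = 33.4, so 34 per arm. Then 34/0.9 = 37.8, so 38 per arm and 76 in total.

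This matches the article and does not bear on the continuous endpoints, for which no sizing is given.

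**Inputs for the check.**
- 40 per arm enrolled and 10% dropout (Sample size calculation): 40 × 0.9 = 36 per arm.
- Two-sided α of 0.05.
- The document gives no SD and no baseline-to-follow-up correlation r. I assume r = 0.3, 0.5 and 0.7, and equal variance σ² at both times.

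**Formulas.** Variance per patient, in units of σ²:
- t-test on final values: 1
- t-test on change scores: 2(1 − r)
- baseline-adjusted model: 1 − r²

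The ratio of adjusted to change-score variance is therefore (1 + r)/2. The difference detectable with 80% power, in SDs of the follow-up value, is √(2/36) × (1.96 + 0.842) = 0.66, multiplied by the square root of the variance above.

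| | r = 0.3 | r = 0.5 | r = 0.7 |
|---|---|---|---|
| Variance, final value | 1.00 | 1.00 | 1.00 |
| Variance, change score | 1.40 | 1.00 | 0.60 |
| Variance, adjusted | 0.91 | 0.75 | 0.51 |
| Saving against final value | 9% | 25% | 49% |
| Saving against change score | 35% | 25% | 15% |
| Detectable difference, final value | 0.66 | 0.66 | 0.66 |
| Detectable difference, change score | 0.78 | 0.66 | 0.51 |
| Detectable difference, adjusted | 0.63 | 0.57 | 0.47 |
| Power at 0.66 SD, final value | 80% | 80% | 80% |
| Power at 0.66 SD, change score | 66% | 80% | 95% |
| Power at 0.66 SD, adjusted | 84% | 90% | 98% |

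At r = 0.5 the saving is worth 1/0.75 = 1.33, or about 33% more patients.

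**Do the two methods give different p-values?** That depends on the model.
- *Treatment only, Gaussian, identity link.* This is the t-test. One simulated data set with 36 per arm gave p = 0.3961 for the t-test, 0.3961 for the linear model, and 0.3932 for the GLM with a Wald z statistic. Nothing material competes, but precision is lost.
- *Baseline included.* The p-values can differ. In 10,000 simulated null trials at each r, with 36 per arm, the chance that a final-value t-test or the adjusted model (or both) gave P < 0.05 was 6.3%, 7.4% and 8.4% for r = 0.3, 0.5 and 0.7. Each test alone stayed near 5% (4.8% to 5.2%). Here the model loses no precision, but there is a choice between two results.

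**The case against.** **The t-test may be meant for description only.** The opening sentence speaks of variables in general. Only the later sentence uses the word outcome, and the χ² test is named again afterwards, which would be redundant if the opening sentence already covered outcomes. On that reading the model governs and nothing conflicts. This is a fair reading, but the text does not settle it: the opening sentence is framed as a comparison of the two arms and is not limited to baseline characteristics. One clause would resolve it.

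**A reader might infer that the plan rules out baseline adjustment.** It does not. The article is silent on the model's covariates, and a condensed article commonly leaves these to the full protocol or SAP. Silence on covariates is therefore not a fault in itself. The point rests on two stated methods without precedence, one of which cannot adjust.

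**A reader might also infer that precision is lost and p-values compete at once.** As shown above, these are alternatives, depending on whether the model contains baseline.

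**A reader might infer bias from chance imbalance.** With 36 per arm the standard error of a baseline difference is √(2/36) = 0.24 SD, so an imbalance above 0.25 SD has a probability of about 29% for any one outcome. But the unadjusted comparison in a randomized trial is unbiased, and its standard error already allows for such imbalance. The issue is efficiency, not validity.

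**The size may be smaller than the largest figure suggests.** If improvement means a change score, baseline is already partly used, and at r = 0.7 the saving is 15%, not 49%. This stands, and both comparators are shown for that reason.

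**Conclusion.** The point holds in limited form. The article names two methods for continuous between-arm comparisons and does not say which decides the continuous secondary endpoints, for which baselines are collected. Under one reading, variance is higher than it need be: adjustment would save 9% to 49% against final values, or 35% to 15% against change scores, as r runs from 0.3 to 0.7. Under the other, two p-values are available for one endpoint, and the chance that at least one falls below 0.05 under the null rises to about 6% to 8%. All these figures rest on assumed correlations, equal variances at both times and 36 evaluable patients per arm. Only secondary endpoints are touched; the primary endpoint has its own test, and the sample size depends on that endpoint alone. The change is worth making because it costs almost nothing, not because the trial's main conclusion is at risk.

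**What to change.** State in the Statistical analysis section that each continuous secondary endpoint (ST depression, Duke score, SF-36, BISF-W, biomarkers) is analysed by one linear model of its scheduled follow-up value on treatment and the baseline value of the same outcome, with centre as an optional further term. Report the adjusted difference with its 95% CI, and limit the t-test to descriptive use.

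For most of these endpoints the scheduled follow-up is week 12. For NT-proBNP and hs-CRP, first reconcile the third footnote of Table 3 (visits 1 and 5) with the blood analysis row (screening and week 12), then model the visit that the corrected chart gives. A continuous perfusion score should not be added to the list as though it were already planned, because Table 1 has no such secondary endpoint.

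The cost is one sentence and one reconciled footnote. Apart from settling the visit for those two markers, no measurement, visit or patient is added.

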### Trial organization

#### Executive committee

The Executive Committee will be composed of the study chairperson and the principal investigators of the investigating centers. This committee will approve the final trial design and protocol issued to the Data and Safety Monitoring Board (DSMB) and the clinical sites. This committee will also be responsible for reviewing the final results, determining the methods of presentation and publication, and the selection of secondary projects and publications by members of the Steering Committee.

#### Data Safety Monitoring Board (DSMB)

An independent DSMB will be composed of cardiologists and a biostatistician following the applicable regulatory guidelines and who did not participate in the trial. The DSMB committee will review the safety data from this study and will make recommendations based on safety analyses of unanticipated device effects (UADEs), serious adverse events (SAEs), protocol deviation, and follow-up reports. In addition to the scheduled DSMB meetings (which will be determined prior to the initiation of the study) the board will convene a meeting at any time if safety problems become an issue. The DSMB are responsible for recommending to the Executive Committee to modify or stop the study if there are any safety or compliance issues. However, the final decision regarding study modifications will rest with the Executive Committee. Cumulative safety data will be reported to the DSMB and will review on an ongoing basis throughout enrollment and follow-up to ensure the safety of the patients. Every effort will be made to allow the DSMB to conduct an unbiased review of the patients’ safety information. All DSMB reports will be made available to the appropriate agencies upon request but otherwise will remain strictly confidential. Prior to the DSMB’s first review of the data, the DSMB charter will be drafted. This plan defines the stopping rules for stopping the trial for safety. The first meeting of the DSMB will be requested for discussion of the protocol and an understanding of all the protocol elements. The DSMB will develop a consensus understanding of all trial endpoints and definitions used in the event adjudication process.

#### Clinical Event Adjudication Committee (CEAC)

The Clinical Events Adjudication Committee (CEAC) is comprised of cardiologists who are not participants in the study. The CEAC is responsible for the development of specific criteria used for the categorization of clinical events and clinical endpoints in the study, which are based on protocol. At the onset of the trial, the CEAC establishes clear rules stating the minimum amount of data required and the algorithm followed in order to classify a clinical event. All members of the CEAC are blinded to the primary results of the trial and meet regularly to review and adjudicate all clinical events in which the required minimum data is available. The committee also reviews and rules on all deaths that may occur throughout the trial.

#### Data coordination and site management

Data coordination and site management services were performed by the Clinical Trials Center at Seoul National University Bundang Hospital.

#### Ethical approval

The study was approved by the institutional review board of each center (Samsung Medical Center Institutional Review Board (approval number 2011-07-048-001), Seoul National University Bundang Hospital Institutional Review Board (approval number B-1106-129-016)) and will be carried out in compliance with the Declaration of Helsinki.

## Discussion

### Treatment option of MVA

There exist several different therapeutic approaches to the treatment of MVA. The primary goal of medical therapy is to ameliorate the chest pain. However, the conventional anti-anginal treatment is often unsuccessful in MVA patients [1]. Lanza *et al*. reported that atenolol was associated with improvement in chest pain episodes, while amlodipine and nitrate were not [15, 16]. Kaski *et al*. reported that angiotensin-converting enzyme inhibition lessens exercise-induced ischemia in MVA patients [17]. Some authors define MVA as a part of visceral pain syndrome which is not related to myocardial ischemia, and reported that imipramine improved the symptoms in MVA patients, possibly through a visceral analgesic effect [18]. Taken together, there exists no standard treatment guideline for MVA.

### Rationale for the use of udenafil in MVA patients

The exact pathogenesis for MVA is unknown. However, it is of note that up to 50% of the resistance to blood flow in the epicardial coronary artery is determined by the small coronary blood vessels [19]. Therefore, small vessels have a significant effect on blood flow in the large vessels. Endothelial dysfunction, inflammation, and microcirculation abnormality are the three most commonly discussed mechanisms for the microvascular dysfunction [20]. Among them, endothelial dysfunction due to an impairment of endothelium-dependent vasodilation due to reduce NO release is the most commonly proposed mechanism for MVA [3]. NO exerts many of the biological actions via cGMP, which is rapidly degraded by cGMP PDE. Thus, PDEi has the potential to improve the endothelial function, which has been shown in animal and clinical studies [7–10].

### Rationale for the udenafil dosage in MVA patients

Udenafil (Zydena™) was developed in 1997 and, after clinical trials, the drug was approved by the Korea Food and Drug Administration (KFDA) in 2005. The commercially available and clinically used doses are 100 mg and 200 mg daily. Its half-life time is between 11 and 13 hours, and the estimated duration of action is approximately 24 hours. Thus, udenafil may be a good candidate drug for chronic use due to its favorable pharmacokinetic properties among PDE-5 inhibitors (sildenafil: T1/2 = 2 hours, duration of action = 4 to 8 hours; tadalafil: T1/2 = 17.5 hours, duration of action = 36 hours). In phase 3 clinical studies [21], the 100 mg and 200 mg doses showed similar efficacy (81 versus 88.5%). However, the side effect rate was lower with 100 mg daily dosing (flushing: 10 versus 23%, headache: 0 versus 23%, chest discomfort: 0 versus 5.4%, and so on).

### Rationale for the safety of udenafil use in MVA patients

A preclinical trial or phase 1 trial with PDE-5 inhibitors in coronary vasculature would minimize the risk of potential candidates being exposed to unnecessary risk. However, there are plenty of studies reporting the safe use of PDE-5 inhibitors in humans, including those evaluating the effect of PDE-5 inhibitors on the coronary arteries in humans[10–12]. There exist at least 11 isoforms of PDE, and the differential distribution of PDE isoforms in various tissues is the basis for the potential tissue-specific effect of a PDE inhibitor. Various tissues have different PDE isoform activities. Corpus cavernosum contains high activities of PDE isoforms 2, 3, and 5; human pulmonary circulation has PDE isoforms 1, 3, 4, and 5; and coronary arteries have PDE isoforms 1, 2, 3, 4, 5 [22]. Consequently, human coronary arteries can be a target of PDE-5 inhibitors.

In clinical trials, sildenafil contributes little to the increase in myocardial flow that occurs during exercise or reactive hyperemia [23], but coronary hemodynamics and circulation are not unfavorably altered after treatment with sildenafil and other PDE-5 inhibitors. These study results imply that PDE-5 inhibitors are safe, but less likely to be effective. Nevertheless, in patients with endothelial dysfunction, the PDE-5 inhibitors would lead to significant hemodynamic improvement. In dysfunctional endothelium, the release of NO by the endothelium is significantly compromised [24]. Halcox *et al*. [25] demonstrated that coronary arterial segments with endothelial dysfunction dilated significantly after application of acetylcholine combined with sildenafil. This finding infers that the inhibition of cGMP breakdown by PDE-5 inhibitors may, at least in part, compensate for reduced NO-related cGMP production due to endothelial dysfunction. Consequently, in patients with MVA with endothelial dysfunction the administration of PDE-5 inhibitors may significantly restore the NO-dependent vasodilation, leading to symptom improvement and improved perfusion in CMR.

Regarding safety concerns, animal studies did not show any coronary steal phenomenon caused by PDE-5 inhibitors [26, 27]. In humans, oral sildenafil produced only small decreases (<10%) in systemic arterial and pulmonary arterial pressures, and it had no effect on pulmonary-capillary wedge pressure, right atrial pressure, heart rate, or cardiac output. Most importantly, sildenafil did not alter coronary flow at rest in stenosed arteries and arteries without angiographically high-grade stenosis, but it increased coronary flow reserve to a similar extent in stenosed and non-stenosed arteries (by 13%), rejecting the possible concern of coronary steel phenomenon [28]. Halcox *et al*. [25] also showed a small beneficial effect on ST-segment depression during exercise testing in patients with known coronary artery disease. These studies demonstrate that coronary hemodynamics and circulation are not unfavorably altered after treatment with sildenafil and other PDE-5 inhibitors; indeed, coronary blood supply may experience a slight improvement. Taken together, there exists clinical data that PDE-5 inhibitors are not harmful in coronary artery patients, and although the effect of PDE-5 inhibitor is limited in normal coronary circulation, in patients with endothelial dysfunction the effect of PDE-5 inhibitors may be clinically significant.

The UMPIRE study is a randomized clinical trial to investigate the cardioprotective properties of udenafil in female MVA patients by means of measuring adenosine-stress perfusion defect size in cardiac MRI. If udenafil improves myocardial perfusion, udenafil may provide a valuable therapeutic option to reduce myocardial ischemia and improve cardiac function in female MVA patients.

### Study limitation

Cardiac syndrome X, or MVA, is generally characterized by patent coronary tree, chest discomfort (typical or atypical angina) with positive evidence of a perfusion defect. Prinzmetal angina patients also complain of chest pain with a normal coronary tree during an attack-free period. Thus, if a pharmacologic provocation test (with ergonovine or acetylcholine, for example) is not performed, there will be a risk for enrolling variant angina patients and this may jeopardize the study. Variant angina patients have distinctive clinical features that may be used to distinguish them from MVA patients. First, the chest pain character differs: while most MVA patients complain of ‘exertional chest pain’, variant angina patients complain of ‘resting chest pain’ which often occurs during early morning and is aggravated by alcohol consumption. Second, variant angina patients do not have vasospasm during an attack-free period. Thus, when performing CMR during an attack-free period, they will have a negative adenosine-stress CMR and will not be enrolled. Third, even if variant angina patients have a coronary vasospasm without chest pain, the perfusion defect in CMR will likely follow a coronary territory, since there exists a clear vessel preference in variant angina patients, mostly involving the right coronary artery. Although we may identify variant angina patients among possible MVA patients by using clinical characteristics and CMR results, we cannot completely exclude the possibility of enrolling variant angina patients. Because the prevalence of variant angina in Asian populationis reported to be between 1 and 5% [14], we will increase the sample size from 70 to 76 patients, in order to achieve scientifically robust results. Despite these measures, the possibility of enrolling patients with variant angina remains a major limitation.

